### **Safety Considerations**

All measurements and interventions are non-invasive and place the subject at no risk other than those that normally may occur during sitting, standing or walking. For some of the participants, particularly those who are not practicing any kind of physical exercise prior to the intervention, there is a slight possibility that they might feel some muscle soreness and fatigue after training. To prevent excessive fatigue, participants will be encouraged to take breaks as needed throughout all study procedures. They will also be advised to consider the potential impact of fatigue on their Parkinson's symptoms when arranging their study visits.

It is possible that technological visual training may cause digital motion sickness (also known as *cyber sickness*), a sensation similar to motion sickness which is caused by moving content on screens. Although this phenomenon is generally related to highly immersive technology (such as virtual reality (VR) headsets), the proposed study will deliver visual training at the most tolerable settings for individuals on the touch screen systems and strobe glasses to further minimise the risk of participants' experiencing these symptoms. A recent study by Kim et. al. (2017) looking at the use of VR by older

adults and PwP during walking showed that they were able to use immersive technology without experiencing adverse effects which provides reassurance that the non-immersive technological training component of the present study should not cause the participants any adverse effects.

The effects of using technology such as stroboscopic glasses as part of a visual training intervention in PwP is not yet known. Commonly recognised effects of prolonged exposure to strobe lighting such as that generated by flickering fluorescent lighting include headaches and eye fatigue, nausea and photosensitive epilepsy. Although participants will only be using the strobe glasses for up to 10 minutes at a time (including breaks), the eligibility criteria for this study has been designed to ensure that individuals who have a history of conditions that are known to be triggered by flashing/strobe lights (such as epilepsy or migraine) will be excluded from the study. Participants will also be given the opportunity to trial the strobe glasses prior to commencing procedures to ensure they can be tolerated. A qualified physiotherapist from the study team will always be with the participant whilst the technology is being used to monitor user-experience and ensure adequate rest periods are taken.

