### **Visual impairments impact gait and balance**

Visual impairments are frequently associated with postural instability and gait disorders in PwP, which increase the risk of falls and lead to loss of independence and a decline in quality of life.

In addition, deficits in the ability to use proprioceptive feedback in PwP result in greater reliance on an impaired visual system to carry out motor tasks. The combination of visual-perceptual deficits and increased visual dependence has a significant impact when accompanied by primary symptoms of Parkinson's such as bradykinesia, rigidity, tremor and postural instability. These impairments reduce a person's ability to compensate and adapt to motor disturbances, which can lead to a decline in functional tasks like walking, rising from a chair, and bed mobility.

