### **Eligibility criteria for participants**

#### ***Inclusion criteria:***

- Clinical diagnosis of Parkinson's by a movement disorder specialist according to UK brain bank criteria (H&Y stage I-III, see *Appendix 3*)
- Aged >50 years
- Able to walk and stand without support or assistance from another person
- Have adequate hearing/vision capabilities to allow participation in all aspects of study (if participant wears prescription glasses, they must be comfortable to remove these for short periods - up to 5 minutes at a time - in order to take part in activities whilst wearing strobe glasses)
- Stable medication for the previous 1 month and anticipated over a period of 6 months.

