### ***Gait and balance assessments***

Participants will stand still and walk in the gait laboratory while wearing several non-invasive wearable sensors that will monitor their balance and gait. Rest breaks will be allowed as needed. Participants will complete several standing and walking tasks in the laboratory, including (but not limited to) walking under single (usual walking) and dual task (speaking while walking) conditions. A researcher will stand / walk close to participants in case of any balance loss.

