### **Group A: Technological Visual Training (TVT)**

The experimental group will receive a total of 8 sessions of TVT over a 4 week period. Each session will last up to 60 min of which 20 mins will be dedicated to a series of visual training drills using a mobile tablet device (see *Appendix 18* for list of training drills), and a further 10 mins will be spent doing simple hand-eye co-ordination activities (e.g. throwing and catching) whilst wearing stroboscopic glasses. The remaining time will be factored in for rest periods as required. Activities will be supervised at all times by the researcher who will keep a running log of issues that may arise during the intervention period such as adverse events, changes in medication or any environmental factors that could affect participant engagement or performance.

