## Appendix 2 – Stroboscopic Glasses and Mobile Training App

[figure not shown]

The Senaptec Strobe glasses and sensory training application are designed to train the connections between an individual's eyes, brain and body.

The mobile application has 14 touch-screen visual training games related to visuo-motor, visual perception, go/no-go, depth perception, tracking etc. These can be done with or without the Strobe glasses.

Liquid crystal technology lenses allow the glasses to flicker between clear and opaque, thereby removing visual information and forcing the individual to process more efficiently.

(<https://senaptec.com/>)

[figure not shown]

The Strobe glasses can connect to a smartphone app via Bluetooth so researchers can adjust the difficulty settings during training. Alternatively, the glasses have buttons on the side so participants can make changes themselves if required.

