#### Hoehn and Yahr Scale

---

- 1: Only unilateral involvement, usually with minimal or no functional disability
  - 2: Bilateral or midline involvement without impairment of balance
  - 3: Bilateral disease: mild to moderate disability with impaired postural reflexes; physically independent
  - 4: Severely disabling disease; still able to walk or stand unassisted
  - 5: Confinement to bed or wheelchair unless aided
-

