## Appendix 20 – Feasibility Outcomes

| Outcome              | Description                                                           | Analysis                                                                                                         |
|----------------------|-----------------------------------------------------------------------|------------------------------------------------------------------------------------------------------------------|
| Safety               | Adverse events (mild, moderate, or severe) caused by the intervention | Total number; compare differences in adverse events between the 2 arms.                                          |
| Amount               | Duration of actual visual training undertaken during each visit       | Compare average duration of visual training tolerated during each one hour visit [min]                           |
| Compliance/adherence | Rate of scheduled and completed sessions                              | Total n sessions completed /total n sessions scheduled (%)                                                       |
| Acceptability        | Motivation

Useability                                          | Pittsburg Rehabilitation Participation Scale Scores (compare mean scores between arms)
System Usability Scale |
| Equipment            | Function of mobile technology in participants' homes                  | Number of issues with equipment, such as break downs, shortage of equipment, internet access                     |

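### The counted safety outcome is narrower than the adverse events recorded, and falls or losses of balance during vision-interrupted work have no clear place in it

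*Protocol*

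**What the plan says.** - **Risk statement.** Safety Considerations opens by saying that measurements and interventions "place the subject at no risk other than those that normally may occur during sitting, standing or walking". Further down, the section says that the effects of strobe glasses in this population have not been established. The harms it names are muscle soreness, fatigue, cyber sickness, headache, eye fatigue, nausea and photosensitive epilepsy. Loss of balance is not among them.
- **Exposure.** Each of the 8 technological visual training (TVT) sessions includes 10 minutes of "simple hand-eye co-ordination activities (e.g. throwing and catching) whilst wearing stroboscopic glasses". Appendix 2 describes the lenses as "thereby removing visual information and forcing the individual to process more efficiently".
- **Population.** Hoehn and Yahr stages I to III are eligible. Appendix 3 describes stage 3 as "mild to moderate disability with impaired postural reflexes".
- **Background.** The section on gait and balance ties visual impairment to postural instability and falls, and reports "greater reliance on an impaired visual system to carry out motor tasks".
- **Laboratory precaution.** For the gait laboratory the protocol states: "A researcher will stand / walk close to participants in case of any balance loss".
- **Recording.** The Adverse Events section records untoward medical occurrences, injuries and clinical signs irrespective of any link to the intervention.
- **Counting.** The Safety row of Appendix 20 defines the outcome as "Adverse events (mild, moderate, or severe) caused by the intervention", totalled and compared between arms. Appendix 21 grades severity by symptoms.
- **Falls.** Falls history belongs to the baseline interview. The FES-I measures fear of falling, not falls.

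**The concern.** Aim 1 asks whether TVT is safe, and the between-arm comparison of adverse events is the quantitative part of the answer. Two statements work against it. The risk statement describes the intervention as adding nothing to everyday movement, while the same section admits that the effects are unknown. The outcome definition then narrows the recorded events to those someone judges to have been caused by the intervention.

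Investigators are not blinded, the researchers deliver the sessions, and no independent adjudicator is named. The restriction to caused events can therefore make the comparison incomplete and dependent on attribution. The events most affected are uninjured falls and near-falls, which are foreseeable when vision is interrupted. A sparse safety table could then be read as support for a larger trial in people at risk of falling.

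**Working it through.** The documents give no fall rate, safety threshold or power figure, and the sample of 40 is expressly not power-based, so there is no plan figure to reproduce. The check is mainly a comparison of passages. The arithmetic after it is illustrative.

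**Passages side by side**

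1. *Risk wording.* The opening sentence of Safety Considerations is a blanket statement about all interventions. The later paragraph says that strobe effects in Parkinson's are unknown. An unknown effect cannot also be asserted to add no risk.
2. *Foreseeability.* People with Parkinson's depend more on vision for motor tasks (background), the glasses interrupt vision (Technological visual training section; Appendix 2), and stage 3 participants are eligible. Loss of balance is therefore foreseeable for at least part of the sample.
3. *Recorded versus counted.* Adverse Events collects everything irrespective of relatedness. Appendix 20 counts only caused events. Feasibility and Safety Analysis plans a chi-square test on adverse events without repeating that restriction, but the Outcomes section names Appendix 20 as the full description.
4. *Grading.* The lowest grade in Appendix 21 is defined by barely noticeable symptoms. A fall without symptoms, or a loss of balance that is caught, has no obvious grade.
5. *Ascertainment.* The running log is described for Group A. The Group B section does not repeat it, although the patient-involvement section mentions a log in general terms.

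**Exposure.** 20 participants × 8 sessions = 160 sessions. 160 × 10 min = 1,600 min, or 26.7 h. This is a ceiling, because Safety Considerations treats 10 minutes as a maximum that includes breaks.

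**Chance of counting at least one affected participant among 20.** Let p be the assumed share of participants with at least one event over the trial, and s the share of those who are counted. The chance is 1 − (1 − p·s)^20. With p = 20%:

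| s | p·s | Chance of at least one counted |
|---|---|---|
| 100% | 20% | 1 − 0.80^20 = 0.988 |
| 50% | 10% | 1 − 0.90^20 = 0.878 |
| 25% | 5% | 1 − 0.95^20 = 0.642 |
| 10% | 2% | 1 − 0.98^20 = 0.332 |

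If none is counted in 20, the one-sided 95% upper limit is 1 − 0.05^(1/20) = 13.9% (16.8% for a two-sided 95% interval). That limit applies to the rate of *counted* events only.

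**Attribution.** Suppose the true share is 20% in both arms, but 50% of affected participants are counted in one arm and 25% in the other. The counted rates are 0.20 × 0.50 = 10% and 0.20 × 0.25 = 5%, an apparent doubling with no true difference. The documents do not show which way such a bias would run.

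**Between-arm test with full counting, 20 against 20, two-sided 5%.** Power is 0.295 by the normal approximation (0.168 by Fisher's exact test) for 5% against 20%, and 0.348 (0.242) for 10% against 30%. The comparison is already weak before any events are lost.

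**The case against.** The case on the other side is substantial.

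- The Adverse Events wording is broad. It clearly takes in injurious falls and can naturally be read to take in others. The severity grades do not set an entry test. This stands, so a reader who inferred that falls go unrecorded would be going beyond the documents.
- TVT activities are supervised throughout with a log that includes adverse events, a physiotherapist is present whenever the technology is used, and participants try the glasses first. This stands too: in-session events under strobe would be witnessed. It does not settle whether they are counted.
- A reader might infer that the protocol classes a stumble under strobe as ordinary risk and therefore leaves it out. No passage gives that rule. The opening sentence does not mention falls, and falling is itself a risk of standing and walking.
- A reader might also infer that the rationale predicts harm. It does not. The background concerns visual impairment from the disease, and the stated premise of strobe training is that it may improve visual-motor control. Throwing and catching is only an example, posture is not stated, impaired postural reflexes describe stage 3 alone, and the number of stage 3 participants is not given. Foreseeable is as far as the text goes.
- The control arm also throws and catches, and its games may use an eye patch (Appendix 19), so the contrast is not strobe against nothing.
- No pilot of this size can exclude rare events, and the event rates used here have no source in the documents.
- The Case Report Form is not shown and may already prompt for falls.

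The conflict inside Safety Considerations, the mismatch between the recording and counting rules, and the absence of falls from the outcome table all survive these points.

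**Conclusion.** The concern holds as a matter of counting and risk wording, not of supervision. The blanket risk sentence conflicts with the admission later in the same section. The Appendix 20 definition is narrower than the recording rule and rests on causal judgement in an unblinded trial. Uninjured falls and near-falls have no clear place in the count. The documents do not support the stronger claim that the safety answer to Aim 1 will miss a harm the protocol predicts.

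The size cannot be derived from the documents. On an assumed 20% of participants affected, counting a quarter of them instead of all lowers the chance of counting any from 98.8% to 64.2%. That figure depends on the assumed rate, the assumed counted share and independence between participants. The change is worth making because it improves the safety comparison at little cost. It does not invalidate the trial.

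**What to change.** 1. Reconcile the opening sentence of Safety Considerations with the later statement on strobe glasses, and name loss of balance during vision-interrupted activity as a foreseeable risk.
2. Reconcile the Safety row of Appendix 20 with the Adverse Events section: compare all recorded adverse events between arms regardless of attribution, and show those judged related separately.
3. Add to Appendix 20, for both arms, the number of participants with (a) at least one fall, or loss of balance needing a grab or staff contact, during a session, and (b) any fall since the previous visit, regardless of injury or attribution. A looser trigger such as any extra step would pick up ordinary movement while catching; the motor scale in Appendix 10 (item 3.12) treats recovery in one or two steps as normal.

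The cost is one line on the session record in both arms and one row in the safety table, with no extra visits or staff. The downsides are slightly more recording, a less favourable safety count, and in-session counts made by unblinded trainers, which should be acknowledged when they are reported.

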#### **Adverse Events:**

Any untoward medical occurrence, unintended disease or injury or any untoward clinical signs in participants whether or not related to the intervention will be recorded as an adverse event and managed according to the Health Research Authority (HRA) Guidance (see *Appendix 21* for a description of adverse events taken from HRA Guidance).

Any serious adverse event (SAE) occurring to a research participant will be reported to the main Research Ethics Committee if the event is related to the administration of the research procedures and unexpected.

Recording of adverse events will start from the signature of the informed consent until the participant has completed or passed through the Day 7  $\pm$  1 days follow-up window. Information and assessments relating to the adverse event will be recorded in the adverse event section of the Case Report Form as per HRA Guidance and will be monitored until resolution or stabilization.

In the unlikely event of any serious adverse event occurring during this study, the University will be informed immediately (and no later than 72 hours after first awareness of the research team) and a written report provided. The university (acting as the Local Sponsor) will follow local reporting guidelines.

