### **ASSESSMENTS**

A repeated measure design will be employed with assessments performed at the clinical gait lab on two separate sessions lasting between 2-3 hours. Participants will attend the lab for outcomes to be measured at the start (baseline) and at the end of the first 4 week intervention. Results will be compared between the groups.

1. Baseline assessment (up to 180 mins)
  - Initial screening and standard clinical assessments
  - Sensorimotor assessment using Senaptec Sensory Station (SSS)
2. Follow-up assessment (after 4 week intervention) (up to 180 mins)
  - Standard clinical assessments
  - Sensorimotor assessment using Senaptec Sensory Station (SSS)

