## **INTERVENTIONS**

Following screening and clinical assessment at the Gait Lab, participants will receive a telephone call from the researcher prior to starting the visits. This will allow participants to ask any further questions about the sessions following their assessments and to help them feel more familiar with the visiting therapist. It will also be an opportunity for the researcher to help the participant identify a suitable location in their home in which to undertake the subsequent training sessions in preparation for the first visit.

After the familiarisation phone call, the home visits will commence. Participants will be allocated to either Group A (technological visual training) or Group B (standard training). Both groups will receive two training sessions per week for four weeks in their home environment delivered by one of the researchers. Following this intervention, participants will be invited back to the Gait Lab for follow-up assessment. See *Figure 1* below for a summary for the study design.

[figure not shown]

Figure 1. Study design

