### **Group B: Standard (non technological) care intervention**

For the standard care group, participants will receive a total of 8 sessions of standard (non-technological) visual training over a 4 week period. As there is currently no accepted “gold standard” visual training approach for use in PwP, the control methodology for this study has been adapted from control conditions used in previous vision therapy trials and traditional therapy practice. Participants will undergo 20 minutes of visual training drills involving a variety of visuo-motor and perceptual tasks (primary pen and paper), followed by a further 10 minutes of games requiring hand-eye coordination skills (e.g. Jenga, throwing and catching). More details of the procedures can be found in *Appendix 19*.

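### Adverse event recording closes at a Day 7 window that has no stated anchor and matches no visit in the readable schedule

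*Protocol*

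**What the plan says.** The Adverse Events section fixes the recording period in one sentence: "Recording of adverse events will start from the signature of the informed consent until the participant has completed or passed through the Day 7". The sentence then gives the tolerance (plus or minus one day) and calls this a follow-up window. Events in the period go into the adverse event section of the Case Report Form.

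The schedule is set elsewhere:

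- ASSESSMENTS has "assessments performed at the clinical gait lab on two separate sessions lasting between 2-3 hours". The first is baseline; the second is described as "Follow-up assessment (after 4 week intervention) (up to 180 mins".
- INTERVENTIONS: "Both groups will receive two training sessions per week for four weeks in their home environment".
- Group A: "The experimental group will receive a total of 8 sessions of TVT over a 4 week period".
- Group B: "participants will receive a total of 8 sessions of standard (non-technological) visual training over a 4 week period".
- Synopsis of Study: follow-up duration is entered as not applicable.

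The Group A section also tells the supervising researcher to "keep a running log of issues that may arise during the intervention period such as adverse events". The Group B section has no matching sentence. Peer Review and Patient and Public Involvement mentions a concurrent log, not limited to one arm, of individual events that could affect the results.

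Feasibility and Safety Analysis (Aim 1) and Appendix 20 make the number of adverse events a feasibility outcome, compared between the two arms.

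**The concern.** A recording window needs a start, an end and an anchor for any numbered day. Here the start is consent, the end is a Day 7 follow-up, and the anchor is missing. Consent is the only time point in the sentence from which Day 7 could be counted. Read that way, or from baseline or the first session, recording stops before most of the training has been given.

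Safety is part of the first aim. The Safety Considerations section says that the effects of stroboscopic glasses in this population are not yet known, and Appendix 18 says that the app's difficulty adjusts upward as people improve. Early sessions need not represent later ones, and events not recorded at the time cannot be reliably recovered at analysis.

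There is a second, separate gap. The instruction to log adverse events throughout the intervention is written for one arm only, although the outcome is a comparison of arms.

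**Working it through.** **Inputs.** Two sessions per week for four weeks in both arms (INTERVENTIONS); 20 participants per arm (SAMPLE SIZE); window end at Day 6, 7 or 8 (Adverse Events). The protocol gives no interval from baseline to the first session; a telephone call comes in between. I assume lags of 1, 3, 7 and 14 days. The spacing of the two weekly sessions is not stated either, so I take every gap from 1 to 6 days.

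**Step 1: the plan's own figure.** 2 × 4 = 8 sessions, as stated for Groups A and B.

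**Step 2: sessions on or before the window end.** With first session on day *f* and within-week gap *g*, sessions fall on days *f* + 7*w* and *f* + *g* + 7*w*, for *w* = 0 to 3. Count those at or before the end day.

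| Day 1 is | End Day 6 | End Day 7 | End Day 8 |
|---|---|---|---|
| First session | 1–2 | 2 | 3 |
| Baseline, lag 1 day | 1–2 | 1–2 | 2 |
| Baseline, lag 3 days | 1–2 | 1–2 | 1–2 |
| Baseline, lag 7 days | 0 | 0 | 1 |
| Baseline, lag 14 days | 0 | 0 | 0 |

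Counting from consent gives the same or fewer sessions than counting from baseline, since consent must precede study procedures.

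- From the first session, 1 to 3 of 8 sessions are covered and 5 to 7 (62.5% to 87.5%) fall outside. At exactly Day 7, 6 of 8 fall outside: 20 × 6 = 120 of 20 × 8 = 160 planned sessions per arm. The window closes at 6/28 to 8/28, or 21% to 29%, of the four weeks.
- From baseline, 0 to 2 of 8 are covered and 6 to 8 (75% to 100%) fall outside.

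**Step 3: the other reading.** If Day 1 is the first session, the eighth session falls on day 22 + *g*, which is day 23 to 28. Seven days after it, plus or minus one, is day 29 (23 + 6) to day 36 (28 + 8). All 8 sessions are covered, but no readable text states this anchor.

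**Step 4: illustration of the stake.** Assume an independent per-session event risk *p* and 20 participants in an arm. Expected events are 20 × sessions × *p*; the chance of recording at least one is 1 − (1 − *p*)^(20 × sessions).

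| Assumed *p* | Expected, 8 sessions | Expected, 2 sessions | Chance of any, 8 sessions | Chance of any, 2 sessions |
|---|---|---|---|---|
| 1% | 1.6 | 0.4 | 80% | 33% |
| 2% | 3.2 | 0.8 | 96% | 55% |
| 5% | 8.0 | 2.0 | about 100% | 87% |

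The values of *p* are not from the protocol; the table shows only how much the choice of anchor can matter.

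**The case against.** The strongest reply is that a harmless reading exists. The protocol uses the term follow-up for one study visit, the assessment after training. INTERVENTIONS places that visit after the intervention without giving a number of days. A Day 7 counted from the last session fits that and loses nothing. Figure 1, the study design diagram, is not visible in the text reviewed and might carry timings. This stands as a possibility. Against it, ASSESSMENTS puts the second visit at the end of the four weeks, the synopsis lists no follow-up duration, and the Adverse Events sentence does not name the last session.

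Serious events are less exposed: the sentence on reporting them to the University covers any occurring during the study and carries no Day 7 limit. A researcher also delivers every session in both arms, so many events would probably be noticed. Both points reduce the practical risk but do not repair the rule for formal recording.

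Two stronger conclusions may tempt a reader, and the protocol supports neither:

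- That most of the exposure will go unrecorded. This follows only if Day 7 is counted from consent, baseline or the first session.
- That the one-arm log biases the comparison against the technological training. If the log counts as adverse event capture, Group A is covered throughout and the early cut-off loses force there. If it does not count, one window applies to both arms. The two harms largely exclude each other, so no direction of bias can be asserted.

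The concurrent log in the patient involvement section is not confined to one arm. However, it concerns events that may affect results, and the same passage still speaks of two four-week intervention periods. It does not stand in for an adverse event instruction in Group B.

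**Conclusion.** The point holds as an internal inconsistency. The end of adverse event recording is tied to a day with no anchor and no matching visit in the readable schedule. Under every reading that counts from consent, baseline or the first session, about 0 to 3 of 8 sessions are covered; under one unstated reading, all 8 are. The range rests on the assumed lags of 1 to 14 days, on any spacing of two sessions a week, and on the unseen figure not defining Day 7.

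This is more than detail that could be left to an analysis plan: the protocol itself sets the rule, and an analysis plan cannot restore events that were never collected. Because the count is an Aim 1 outcome compared between arms, the rule should be corrected. Whether events would be lost in practice, and in which arm, cannot be determined from the text.

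**What to change.** Reconcile the Adverse Events section with ASSESSMENTS and INTERVENTIONS:

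1. State one recording period, identical in both arms, from consent to at least the post-intervention follow-up assessment. If Day 7 was meant to run from the last session or the final assessment, say so and keep it as a stated number of days after that point. Simply deleting the window could shorten recording if this was the intention.
2. Keep an end rule for participants who do not attend the follow-up assessment. The present wording provides one by closing recording once the window has passed.
3. In the Group B section, state that the running adverse event log described for Group A applies there too.

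With recording through the follow-up assessment, coverage is 8 of 8 sessions under any session spacing. The cost is about one sentence under Adverse Events and one under Group B. No visit is added, because a researcher already delivers every session in both arms.
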